### Baseline examination

The following data are collected during the baseline examination: Date; patient age, sex, and contact information; left or right knee, symptoms, and current treatment; medical history; clinical examination findings, including range of motion, stability tests (Lachman, pivot-shift, and posterior drawer tests); meniscus signs; intra-articular effusion; soft-tissue swelling; circumference measurements; and leg axis, including intercondylar and intermalleolar distances.

### Data processing

Patient name and contact information, along with the results of the baseline examination, are transmitted to the evaluation center (Martin Luther Hospital, Berlin). After evaluation, the data are processed anonymously. Any publication of the data is also done anonymously.

### Outcome parameters

Primary outcome measures are subjective assessments of recovery using a seven-point Likert scale
[29,37] at 3 months and 1 year. This parameter was used for the sample size calculation.

Secondary outcome measures are subjective assessment of recovery using a seven-point Likert scale at 6 weeks; modified functional Kujala score
[39] without the parameters muscular atrophy and flexion; the German version of the Knee Injury and Osteoarthritis Outcome Score (KOOS)
[40,41]; pain at rest and with walking, stair climbing, sitting and sports activity, reported on a numerical scale (0 to 100); and review of compliance and additional interventions. All these measurements are evaluated via questionnaire at baseline, 6 weeks, 3 months and 1 year.

The seven-point (*completely recovered, strongly recovered, significant improvement, moderate improvement, little improvement, slightly recovered, worse than ever*) Likert scale used in the present study was used previously by Van Linschoten et al.
[29] to study the effect of supervised physiotherapy on PFPS patients (Table 
1). Patients were deemed to have recovered if they rated themselves *fully recovered* or *strongly recovered*, whereas those who rated themselves *slightly recovered* to *worse than ever* were deemed not to have recovered. This threshold was used to dichotomize perceived recovery into two clear categories: “recovered” and “not recovered”.

**Table 1 T1:** Seven-point Likert scale used to measure recovery

	**1**	**2**	**3**	**4**	**5**	**6**	**7**
**German (original version)**	Komplette Heilung	Fast geheilt	Deutliche Besserung	Mäßige Besserung	Wenig Besserung	Geringfügig gebessert	So schlecht wie bisher
**English translation**	Completely recovered	Strongly recovered	Significant improvement	Moderate improvement	Little improvement	Slightly recovered	Worse than ever

Patients were classified to have recovered if they rated themselves *fully recovered* or *strongly recovered.* Those who rated themselves as *slightly recovered* to *worse than ever* were classified as not recovered.

The Kujala score is a disease-specific, validated disability scale for patellofemoral disorders that ranges from 0 (complete disability) to 100 (fully functional)
[39].

The validated German version of the KOOS is self-explanatory and consists of five subscales; pain, symptoms, sports/recreational activities, activities of daily living, and function
[40]. Standardized answer options are given (five Likert boxes), and each question is assigned a score from 0 to 4. A normalized score (100 indicating no symptoms and 0 indicating extreme symptoms) is calculated for each subscale
[40,41]. A total score has not been validated and is not recommended
[40].

Pain at rest and with walking, stair climbing, sitting, and sports activity is marked by the patient on a numerical scale (0 to 100).

All patients are asked during telephone interviews at 6, 12, and 54 weeks if they have adhered to treatment. It is noted if they have not continued using the brace, performed the home-exercise program, or attended supervised physiotherapy sessions.

### Expected results

In the study of Clark et al.
[37], functional recovery was significantly higher in a group of PFPS patients who performed supervised physiotherapy. We hypothesize that the passive realignment provided by the Patella Pro brace decreases pain during exercises. Therefore, we expect that the exercises in group 2 are more effective than in group 1. This should result in a significantly higher rate of recovery in group 2.

Van Linschoten et al.
[29] observed a decrease in pain at rest and with activity as well as an increase in function after 3 months in a group receiving supervised physiotherapy. Therefore, decreased pain and increased function are also expected in all patients in the present study. The hypothesis of this study is that patients using the brace will experience greater improvements (higher scores) in the KOOS subscales and Kujala score and greater reductions in pain than non-braced patients.

### Statistical analyses

To evaluate additional effects of the patellar brace on supervised exercise and home exercise in patients with PFPS, between-group differences in clinical outcomes will be analyzed on the basis of intention to treat. Logistic regression techniques are used for dichotomous outcome parameters. Continuous outcomes will be analyzed with linear regression techniques. Recovery, as measured by the seven-point Likert scale, will be dichotomized to recovered (fully or strongly) or not recovered (slightly to strongly worsened). Other outcome measures will be analyzed as continuous variables.

Statistical analyses are performed at Medistat, Kiel, Germany.

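### The recovered/not-recovered rule for the primary endpoint leaves scale categories 3, 4 and 5 in neither class, and its end point in the Statistical analyses section is not a category on the scale

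*Protocol article*

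**What the plan says.** The Outcome parameters section names the endpoint: "Primary outcome measures are subjective assessments of recovery using a seven-point Likert scale", at 3 months and 1 year. It adds that this parameter was the basis of the sample size calculation.

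The section lists the categories in order: "completely recovered, strongly recovered, significant improvement, moderate improvement, little improvement, slightly recovered, worse than ever". Table 1 numbers them 1 to 7 in the same order.

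The classification rule is stated three times:

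- Outcome parameters, running text: "Patients were deemed to have recovered if they rated themselves *fully recovered* or *strongly recovered". The same sentence gives the not-recovered class as *slightly recovered* to *worse than ever*.
- Table 1 note, after the same definition of recovered: "Those who rated themselves as *slightly recovered* to *worse than ever* were classified as not recovered".
- Statistical analyses: "Recovery, as measured by the seven-point Likert scale, will be dichotomized to recovered (fully or strongly) or not recovered (slightly to strongly worsened".

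Of the rule, the Outcome parameters section says: "This threshold was used to dichotomize perceived recovery into two clear categories". The Statistical analyses section specifies logistic regression for dichotomous outcomes, on the basis of intention to treat.

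**The concern.** A binary endpoint needs every possible answer to fall into exactly one class. Here three of the seven answers, including all three labelled as improvement, fall into neither. The Statistical analyses section, which an analyst would work from, also ends the range at a label that no patient can tick.

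This is the primary endpoint and the basis of the sample size. Followed to the letter, the rule removes randomised patients from the primary analysis because of what they answered. That is selection on the outcome and conflicts with intention to treat. Any imbalance between the arms in the share answering 3–5 would then distort the comparison. If the gap is instead filled informally, the choice could be made after the data have been seen. The Expected results section anticipates less pain and better function in all patients, so answers in 3–5 may well be common; this is an inference, as the document gives no distribution.

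**Working it through.** **Step 1. Map the rule onto Table 1.**

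| Category | English label | Class under the written rule |
|---|---|---|
| 1 | Completely recovered | Recovered (if *fully* means *completely*) |
| 2 | Strongly recovered | Recovered |
| 3 | Significant improvement | None |
| 4 | Moderate improvement | None |
| 5 | Little improvement | None |
| 6 | Slightly recovered | Not recovered |
| 7 | Worse than ever | Not recovered |

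Four of seven categories are assigned and three are not. Neither *fully recovered* nor *strongly worsened* is a Table 1 label. The first is an obvious synonym of category 1; the second matches nothing on the scale.

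**Step 2. Check the plan's own sample size.** The Sample size calculation section gives a 22-point difference, alpha 0.05, power 0.80 and 135 patients before dropout. It gives neither recovery rate, so 135 can be neither confirmed nor refuted. With the two-sided pooled-variance formula

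n per arm = [1.96·√(2p̄(1−p̄)) + 0.842·√(p₁(1−p₁) + p₂(1−p₂))]² / d²

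the total for a 22-point difference runs from 86 (5% v 27%) to 160 (39% v 61%). Two rate pairs come close to 135:

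- 20% v 42%: p̄ = 0.31, n = (1.282 + 0.535)² / 0.0484 = 68.2, so 69 per arm and 138 in total.
- 58% v 80%: the mirror image, also 138.

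At 67.5 per arm (135 in total), each pair has 79.6% power. These pairs are assumptions chosen to fit the plan.

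**Step 3. Leave out the unassigned categories.** Let m be the share of patients in categories 3–7 who answer 3, 4 or 5, assumed equal in both arms. The share of an arm still analysed is 1 − m(1 − p), and its recovery rate becomes p / [1 − m(1 − p)]. Power is Φ[(d − 1.96·s₀)/s₁], with s₀ = √(p̄(1−p̄)(1/n₁+1/n₂)) and s₁ = √(p₁(1−p₁)/n₁ + p₂(1−p₂)/n₂).

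Worked case, 20% v 42% and m = 0.5:

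- Analysed shares are 1 − 0.5×0.80 = 0.60 and 1 − 0.5×0.58 = 0.71, so n = 40.5 and 47.9.
- Rates are 0.20/0.60 = 33.3% and 0.42/0.71 = 59.2%, with weighted p̄ = 0.473.
- s₀ = 0.1066 and s₁ = 0.1026, so (0.2582 − 0.2089)/0.1026 = 0.48, which gives power of 68%.

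| Assumed rates, 1–2 v 3–7 | m | Patients analysed, of 135 | Rates after exclusion | Power |
|---|---|---|---|---|
| 20% v 42% | 0 | 135 | 20% v 42% | 80% |
| 20% v 42% | 0.5 | 88 | 33% v 59% | 68% |
| 20% v 42% | 0.8 | 60 | 56% v 78% | 47% |
| 58% v 80% | 0 | 135 | 58% v 80% | 80% |
| 58% v 80% | 0.5 | 114 | 73% v 89% | 57% |
| 58% v 80% | 0.8 | 102 | 87% v 95% | 31% |

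If 3–7 are all classed as not recovered, nobody is left out and nothing is lost.

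**The case against.** The best defence is that the intent can be read from the text. All three statements give the same closed list for recovered. The Outcome parameters section calls the rule a threshold that yields two clear classes, and the Statistical analyses section speaks of dichotomising under intention to treat. A single cut below category 2 on an ordered scale puts 3–7 in not recovered, and dropping 3–5 would contradict all of this. That argument stands as to intent. It does not repair the rule: the written range starts at category 6 in the text and in the Table 1 note, and no sentence assigns 3–5.

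The same argument limits how far the point can be pushed. A reader might infer that:

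- The endpoint cannot be computed at all. The text supports only that it is not properly defined as written, since the likely meaning is recoverable.
- An analyst would be free to count *significant improvement* as recovered. The closed list, given three times, excludes that. The open question is whether 3–5 are dropped or counted as not recovered.
- The rule was carried over from a scale with other steps. Nothing in the article shows this, and it says that the cited study used this scale.

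It is also fair to object that the power figures rest on assumed rates and on an assumed share in 3–5. They do, and they are offered only as a range.

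**Conclusion.** The point holds as a fault in the written definition of the primary endpoint. Categories 3–5 have no class in any of the three statements, and the Statistical analyses section uses an end label that is not on the scale. Because the article states the rule explicitly and gets it wrong, this is not detail left to a fuller protocol or analysis plan. It should be corrected before the groups are compared.

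If the rule were applied literally, power would fall from about 80% to about 57–68% with half of categories 3–7 left out, and to about 31–47% with 80% left out. This assumes 20% v 42% or 58% v 80%, 135 evaluable patients, a two-sided test and the same share left out in both arms. Under the probable intent, no power is lost.

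A secondary point concerns category 7. Its German label, "So schlecht wie bisher", means as bad as before, not *worse than ever*. A reader might infer that this distorts the primary result. It does not: Table 1 gives the German wording as the original version, and category 7 is not recovered under either label.

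**What to change.** In the Outcome parameters section, the Table 1 note and the Statistical analyses section, define the classes by number: recovered = category 1 or 2; not recovered = categories 3 to 7; no category excluded. Use the Table 1 labels throughout, so *completely* in place of *fully*, and delete *strongly worsened*. As a lesser edit, change the English label of category 7 to *as bad as before*.

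The cost is a few words in three places, with the same definition in any analysis plan, before any unblinded analysis. No new data are needed, and neither the questionnaire nor the sample size changes.

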## Discussion

The Patella Pro study was designed after reviewing the literature on therapy for patients with PFPS
[9,29]. The PEX study protocol published by Van Linschoten et al.
[9] served as the model for this trial because it is a high-quality protocol for a trial examining an intervention for patients with a PFPS.

Treatment options for PFPS patients are patellar taping and bracing
[7]. The exact mechanism of action of both modalities is unknown. Some authors have been able to demonstrate biomechanical effects of taping and brace application; others have demonstrated improved proprioception and effects on brain activity
[30,31]. A meta-analysis of studies limited in number and quality has shown that brace therapy may have a positive effect on PFPS
[33]. Conflicting results of studies of the effects of patellar bracing
[33] could also be the result of the brace design. The present study will contribute to the elucidation of this research question. We expect an answer about the clinical effect of the Patellar pro brace for the treatment of PFPS. Unfortunately we cannot answer if the effect is due to the medially directed force or a proprioceptive effect.

Based on the available literature regarding tape application in PFPS patients
[33,42,43], our research group expects to discover benefits of brace treatment, including perceived recovery and improvements in pain severity and functional disability, in the Patella Pro study.

A limitation of the present study design is that only patients with an existing MRI and x-ray are included. This could be a selection bias, as only those patients with greater attention to their pathological condition are selected. Another limitation could be the age band going up to 50 as this group may have other symptoms. However, the exclusion criteria will mediate against some of these.
